### Sample size calculation

2.8

To the best of our knowledge, no study has investigated cerebral changes between connected and disconnected consciousness using fMRI. Hence, no effect size was available in the literature for a power calculation with a similar setup as the current experiment. However, we were able to make an approximate estimate of the total sample size required based on EEG studies investigating sensory disconnection during propofol anesthesia (Casey et al., 2022a), REM (own data, to be submitted) and NREM sleep (own data, to be submitted). We estimated the effect size with Cohen’s *d* from the means and standard deviations of each group, and we performed power calculations (two tailed t-tests) by setting the desired α at 0.05 and power at 0.95. In the first study conducted under propofol sedation, the effect size of the difference between CC and DC in occipital delta power was 1.0 and the allocation ratio N2/N1 was 2.78. In the REM and NREM sleep studies, the effect size of the difference between CC and DC in event related potentials was 0.85 with allocation ratio N2/N1 = 1 and 0.94 with allocation ratio N2/N1 = 0.71, respectively. The total estimated sample size is of 70 sessions according to power calculations based on the effect size of the propofol study; of 64 sessions based on the effect size of the NREM study and of 74 sessions, based on the REM study’s effect size (see Figure 5). Taking the most conservative estimate based on the smallest effect size of the three studies, and accounting for an 8% dropout (e.g., impossible to reach LOR or ROR), we plan to collect 40 subjects, for a total of 80 sessions (two per subject). This power analysis was conducted in G*Power 3.1.9.7 software (Faul et al., 2007, 2009) and the results plotted in MATLAB.

**Figure 5 fig5:**
[figure not shown]
Results of the power analysis based on the effect sizes obtained from three studies investigating the difference between connected and disconnected consciousness using EEG. Estimated total sample sizes for power 0.6–0.95 are shown for each of the effect sizes reported in the studies conducted under propofol sedation [yellow circles; Casey et al. (2022a)], during NREM (blue circles) and REM (green circles) sleep. α err prob. = 0.05.

### Preprocessing and statistical analysis

2.9

As we will use a mixed block/event-related design, all the following analyses (see Table 1 for a summary) will be conducted on the BOLD time-series at both the block and trial level: for the block-level analyses, we will contrast (1) task blocks (i.e., standard and deviant blocks combined) with silence blocks and (2) standard vs. deviant blocks. For the trial-level analysis, we will contrast (1) combined deviant and standard trials with BOLD extracted time-series of simulated time points during silence blocks and (2) deviant vs. standard trials. For the purpose of this project and the hypotheses presented, the analysis of RS data will not be discussed in this study.

**Table 1 tab1:** Hypotheses tested and corresponding analyses. This table provides a comprehensive overview of the analyses, brain areas, atlas employed, and statistical methods used for each hypothesis tested in this study.

Hypotheses tested	Analyses	Considered brain areas	Atlas	Statistical analysis
*Hypothesis 1*	Activation analysis (ROI-based)	All 7 sub-thalamic regions (L/R)	Oxford thalamic connectivity atlas	Small volume correction
*Hypothesis 2*	Activation analysis (ROI-based)	Primary auditory cortex (L/R): Heschl’s gyrus	Harvard-Oxford cortical and subcortical structural atlases	Small volume correction
*Hypothesis 3*	Activation analysis (ROI-based)	Secondary regions (L/R): superior temporal gyrus (both anterior and posterior division)	Harvard-Oxford cortical and subcortical structural atlases	Small volume correction
*Hypothesis 4*	ROI-to-ROI based connectivity	2 sub-thalamic (sensory and temporal) nuclei and Heschl’s gyrus	Oxford thalamic connectivity atlas/ Harvard-Oxford cortical and subcortical structural atlases	Subject-level: wGLM Group-level: LME
*Hypothesis 5*	ROI-to-ROI based connectivity	Heschl’s gyrus and superior temporal gyrus (both anterior and posterior division)	Harvard-Oxford cortical and subcortical structural atlases	Subject-level: wGLM Group-level: LME
*Hypothesis 6*	Voxel-to-voxel connectivity	Whole cortical and subcortical brain matters	No atlas	Subject-level: Intrinsic connective analysis Group-level: LME
*Hypothesis 7*	Spectrogram analysis	All 7 sub-thalamic regions (L/R); Primary auditory cortex (L/R): Heschl’s gyrus; Secondary regions (L/R): superior temporal gyrus (both anterior and posterior division)	Oxford thalamic connectivity atlas; Harvard-Oxford cortical and subcortical structural atlases; Harvard-Oxford cortical and subcortical structural atlases	Subject-level: Short Time Fourier Transform (STFT) for regional spectrogram estimation. Group-level: LME

#### Preprocessing

2.9.1

fMRI data will be preprocessed in software SPM12 (Statistical Parametric Mapping, version 12, UCL Institute of Neurology, London, Britain, http://www.fil.ion.ucl.ac.uk/spm) and FSL 6.^3^ The preprocessing pipeline will include standard steps of realignment, susceptibility-induced distortions correction [FSL topup (Andersson et al., 2003; Smith et al., 2004)], slice acquisition time correction, coregistration, brain tissue segmentation, spatial normalization to the Montreal Neurological Institute stereotaxic template and smoothing using the Gaussian filter method with an isotropic kernel of size 6 mm. Outlier volumes, due to excessive head and body motion, will be detected using Artifact Detection Tools (ART) toolbox^4^ and will be regressed out in the first-level general linear model (GLM) analysis. An image will be defined as an outlier image or artifact if the absolute head displacement in the x-, y-, or z-direction is equal or greater than 2.3 mm, if the framewise displacement is greater than 0.4 mm, or if the overall average image intensity is greater than 3 standard deviations from the average intensity of the rest of the images. For each run of the 15-min auditory paradigm, the first five volumes will be discarded to allow magnetization to reach dynamic equilibrium.

#### Connectivity analyses (ROI-ROI, Hypothesis 4-5)

2.9.3

Before carrying out the connectivity analysis, functional data will be denoised using a standard denoising pipeline (Nieto-Castanon, 2020) including the regression of potential confounding effects characterized by 5 principal components of white matter and cerebrospinal fluid using the component-based noise correction method (CompCor), 6 motions parameters and their 6 motions parameters and their first order derivatives, outliers volumes, session and task effects and their first order derivatives and linear trends within each functional run, followed by high pass filtering above 0.008 Hz. To assess task-related functional connectivity changes across experiment blocks/trials, the pair-wise ROI-ROI connectivity will be estimated as bivariate correlations using a weighted general linear model (wGLM) as implemented in CONN. The boxcar signal characterizing each block/trial, convolved with an SPM canonical hemodynamic response function and rectified, will be used to weight the ROI signals in the wGLM model. This will lead to block/trial-specific between-ROI correlation coefficients which will be then Fisher-transformed for further analysis. The ROIs will include two sub-thalamic (sensory and temporal) nuclei and the Heschl’s gyrus (hypothesis 4) and superior temporal gyrus (both anterior and posterior division; hypothesis 5). The results of this step would be connectivity matrices at the subject-level showing the correlation between the defined ROIs.

#### Connectivity analyses (voxel-voxel, Hypothesis 6)

2.9.4

Data will be denoised as described in the previous paragraph. An exploratory analysis will be conducted at the whole-brain level, estimating the intrinsic connectivity maps related to each block/trial as implemented in CONN. This parameter characterizes network centrality at each voxel as the root mean square (RMS) of all short- and long-range connections between a voxel and the rest of the brain (Martuzzi et al., 2011).

#### Group-level analysis

2.9.5

For group-level activation analysis (block/trial) we will perform a linear mixed effect model with nested random effects of subjects within the two experimental sessions, using package lme4 in software R. Fixed effects will be included to control for condition (CC vs. DC), stimulus/block type (deviant vs. standard or silence vs. sound), interaction between stimulus/block type and condition, propofol concentration and time to ROR. The latter allows the investigation of the effect of extending reports back in time, i.e., it is more probable that the subject was in a CC/DC state shortly before awakening as opposed to a long time before awakening. For the group-level connectivity analysis the same procedure will be followed, considering the connectivity matrices or intrinsic connectivity maps as dependent variables.

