### Experimental setup

2.2

In short, the present experiment will comprise four main phases (schematic representation in Figure 2): (1) acquisition of MRI data in awake participants during rest and auditory stimulation, (2) gradual sedation with propofol (~45 min), (3) training session of sedated participants for ~20 min (see below for an explanation) and (4) acquisition of MRI data in sedated participants during rest and auditory stimulation, both repeated twice. During the awake phase a structural (T1) image will be collected prior to the acquisition of functional scans during rest (~10 min) and auditory stimulation (~15 min; for a detailed description of the auditory paradigm, see the section “fMRI experimental design and auditory paradigm”). To prevent the comparison of connected and disconnected consciousness from being contaminated by correlates of (un)responsiveness we will ensure that participants were unresponsive prior to the start of the experimental sessions and awakening. We will also assess their state of wakefulness before and after the experimental sessions to minimise the risk of arousals and confounding correlates of wakefulness with those of (dis)connected consciousness.

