
LOR1 will mark the beginning of the experimental session. After LOR1, we will acquire 10 min of resting-state (RS) fMRI followed by 15 min of task-based fMRI, i.e., passive listening to a sequence of oddball auditory stimuli. After concluding the fMRI acquisition and without altering the drug concentration, we will attempt to awake participants by performing the arousal protocol described above. If the participant does not regain responsiveness after one execution, the protocol will be repeated a maximum of two times. If the participant does not regain responsiveness after three executions, the participant will be defined unarousable. In case of ROR, participants will be questioned about their experience during the period of unresponsiveness to determine whether they were (un)conscious and (dis)connected (see “interviews following ROR”). After the first ROR (ROR1), we will wait a maximum of 10 min for the participant to spontaneously lose responsiveness a second time (LOR2). If the participant does not lose responsiveness in the 10 min following ROR1, we will increase the propofol concentration up to three times in 0.1 μg.ml^−1^ increments. If, after increasing the concentration, the participant does not reach LOR2, the LOR attempt will be considered unsuccessful, and the experiment will be terminated. In the case that LOR2 succeeds, the procedure described above for ROR1 will be repeated for ROR2. Finally, the end of the experiment is marked by termination of the drug infusion. This protocol has been fine-tuned based on previous work of our team (Bonhomme et al., 2016).

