### Variables of interest, randomization, and blinding

2.7

In this experiment, the dependent variable will be the BOLD signal (during RS/task sessions). The independent variables will be both the connected/disconnected condition and the type of sounds delivered, i.e., standard or deviant events or silence. The connected/disconnected condition cannot be randomized, given its unpredictability, i.e., it is impossible to predict which individuals will report being connected and which will report being disconnected. In contrast, several parameters of the auditory paradigm will be randomized (e.g., the number of repetitions of standard events). Similarly, the temporal order of the waking and sedation sessions cannot be randomized given the use of anesthetics: data acquisition after the end of sedation would in fact correspond more to acquiring data during the recovery than during the awakening phase. Finally, the order of the RS and task sessions will not be randomized due to time constraints: since the collection of reports must occur immediately after the task session, if the task preceded the RS session, we would be forced to collect reports after the task and then wait for the participants to lose responsiveness again to acquire the 10 min of rs-fMRI, considerably extending acquisition time. Data preprocessing and analysis will be performed blind to the conditions of the experiment.

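### The group-level mixed model nests subjects within sessions, the reverse of the design, so the CC vs DC main-effect test has no term linking a participant's two sessions

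*Protocol article*

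**What the plan says.** Section 2.9.5 of the protocol article says of the group-level activation analysis: "we will perform a linear mixed effect model with nested random effects of subjects within the two experimental sessions". The software named is lme4 in R. On the fixed part it says: "Fixed effects will be included to control for condition (CC vs. DC), stimulus/block type (deviant vs. standard or silence vs. sound". The list goes on to the interaction of these two, propofol concentration and time to ROR. It has no subject term and no session-order term. Connectivity is covered by reference: "For the group-level connectivity analysis the same procedure will be followed". Table 1 names an LME at group level for H4 to H7 but gives no random-effects structure.

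The design is described in three other places. Section 2.2 lists "acquisition of MRI data in sedated participants during rest and auditory stimulation, both repeated twice" as the fourth phase, and says of the second loss of responsiveness that "the procedure described above for ROR1 will be repeated for ROR2". Section 2.8 says "we plan to collect 40 subjects, for a total of 80 sessions (two per subject". Section 2.7 explains that the state cannot be assigned, because "it is impossible to predict which individuals will report being connected and which will report being disconnected".

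**The concern.** Sessions sit inside subjects, but section 2.9.5 puts subjects inside sessions. In lme4 notation the literal reading is (1|session/subject), which expands to (1|session) + (1|session:subject). The first term is a random effect with two levels shared by everyone. The second is a separate, independent effect for each participant in each session. Neither lets one person's two sessions resemble each other more than two sessions from different people.

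State is classified session by session from the interview, so a participant may be CC twice, DC twice, or one of each. If states repeat, two correlated sessions count as two independent pieces of evidence and the standard error is too small. If states switch, each participant is their own control, the model does not use this, and the standard error is too large. The mix is known only after data collection, so neither the direction nor the size of the error is known in advance.

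**Working it through.** **1. Inputs.** From section 2.8: 40 subjects, 80 sessions, two per subject; two-tailed t-tests, α = 0.05, power 0.95; the smallest effect size, d = 0.85 with allocation ratio 1 (REM study), requiring 74 sessions; 8% dropout. Assumed, because the article does not give them: the between-session correlation ρ within a person (0 to 0.7), and the share s of participants whose state changes between sessions (0 to 1). Total variance is set to 1.

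**2. The plan's own figure.** A two-sided independent-samples t-test with d = 0.85 and 37 + 37 sessions has power 0.950, so 74 reproduces. 74 × 1.08 = 79.9, which gives the planned 80. The count treats sessions as independent, so the sample size does not carry the within-person link either. The checks below use 74 sessions as 37 complete pairs.

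**3. Standard error under the literal nesting.** With 37 CC and 37 DC sessions taken as independent, SE = √(1/37 + 1/37) = 0.232, whatever ρ and s are. If nobody changes state, 19 subjects in one state and 18 in the other give 38 and 36 sessions, and SE = √(1/38 + 1/36) = 0.233.

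**4. True standard error of that same estimate, ρ = 0.5.**
- All change: √(2(1 − 0.5)/37) = 0.164.
- Half change (19 switch, 9 CC twice, 9 DC twice): √([19 × 2 × 0.5 + 18 × 2 × 1.5]/37²) = √(73/1369) = 0.231.
- None change: √(1.5 × (1/38 + 1/36)) = 0.285.

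**5. Type I error.** The ratio of true to modelled variance is 1 + ρ(1 − 2s), so the type I error at nominal 5% is about 2[1 − Φ(1.96/√(1 + ρ(1 − 2s)))].

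| ρ (assumed) | none change | half change | all change |
|---|---|---|---|
| 0 | 0.050 | 0.050 | 0.050 |
| 0.3 | 0.086 | about 0.05 | 0.019 |
| 0.5 | 0.110 | about 0.05 | 0.006 |
| 0.7 | 0.133 | about 0.05 | below 0.001 |

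Between these points, at ρ = 0.5: s = 0.25 gives 1.96/√1.25 = 1.753, type I error 0.080; s = 0.75 gives 1.96/√0.75 = 2.263, type I error 0.024.

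**6. Precision lost when half change.** The test is then about correctly sized, but the estimate ignores the pairing. With a shared subject effect at ρ = 0.5, the 19 switching pairs contribute information 19/(2 × 0.5) = 19. The 9 + 9 non-switching pairs contribute 1/(0.75 × 2/9) = 6. So SE = 1/√25 = 0.200, against 0.231.

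**7. Check by fitting both models.** REML simulation with two stimulus types per session, subject variance half of the total, and 150 runs per scenario (Monte Carlo error about 0.02):

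| Change of state | (1\|session/subject): SE, type I | (1\|subject/session): SE, type I |
|---|---|---|
| all | 0.217, 0.007 | 0.140, 0.067 |
| half | 0.215, 0.033 | 0.174, 0.053 |
| none | 0.215, 0.107 | 0.270, 0.073 |

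The literal model reports nearly the same SE in all three rows. The model with sessions inside subjects adapts.

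**8. Incomplete pairs.** Suppose 60% of participants give two usable sessions and 40% give one (assumed). The share of sessions belonging to a pair is then 1.2/1.6 = 0.75. With no change of state and ρ = 0.5 the variance ratio is 1 + 0.5 × 0.75 = 1.375, and the type I error falls from 0.110 to 0.095.

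**9. Interaction.** Stimulus type varies within a session, so a random intercept at subject or session level cancels from the stimulus contrast. In a balanced layout with two stimulus levels per session, the interaction's SE was the same under either nesting and its type I error was 0.050 in every scenario checked.

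**The case against.** The article gives prose, not a model formula, and its sample-size section shows that the authors know each subject has two sessions. The sentence may simply be a slip for the reverse nesting. That stands as a caution, so the point is put on the text as written. It does not remove the point, because nothing else in the article states the hierarchy correctly and an analyst following section 2.9.5 would fit the wrong model.

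Several stronger readings are tempting and are not supported:
- *Type I error is inflated to 9–13%.* That holds only if no participant changes state, at assumed correlations of 0.3 to 0.7 and with complete pairs. If about half change, the test is roughly the right size; if more do, it is conservative. The article gives neither quantity.
- *All of H1 to H6 are compromised.* Silence vs sound by condition is a natural test for H1 to H3, and deviant vs standard by condition is the substance of H6. Both are interactions formed within a session, and the intercept nesting largely leaves them alone. If stimulus effects themselves correlate across a person's sessions, a random intercept in either order would not capture it.
- *H7 uses this model.* Section 2.9.5 covers activation and connectivity. For H7, Table 1 says LME without a structure and section 2.9.6 says only that the peak-frequency series will be compared.
- *All 40 subjects give two usable sessions.* Section 2.3 discards awakenings without recall and excludes reports of being awake. Section 2.2 allows for unarousable participants and a failed second loss of responsiveness. Unpaired sessions dilute the error.
- *A two-level random session effect cannot be fitted.* It can, but its variance is poorly estimated. Propofol concentration is already a covariate, so part of what session order might carry is adjusted for.

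**Conclusion.** The stated random-effects structure reverses the design and should be corrected before analysis. The consequence falls on the CC vs DC main effect: chiefly H4 and H5, where connectivity is predicted to be stronger in CC, and any activation main effect of condition. At an assumed correlation of 0.5 with 37 complete pairs, the type I error runs from about 0.11 (nobody changes state) through about 0.05 with an SE of 0.231 instead of 0.200 (half change) to about 0.006 (all change). With no change of state it is 0.086 at correlation 0.3 and 0.133 at 0.7. The error vanishes at zero correlation and shrinks as the share of participants with a single usable session grows. These sizes rest on an assumed correlation and an unknown mix of states. That the nesting is the wrong way round rests on the text alone.

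**What to change.** In section 2.9.5, state that sessions are nested within subjects: (1|subject/session) where a session supplies several values, or (1|subject) where it supplies one. Enter session (LOR1 or LOR2) as a fixed effect instead of a two-level random factor. Say that the same structure applies to the connectivity models, and state the random effects for the H7 LME listed in Table 1. The cost is about one sentence and a matching entry in the table. No new data are needed, and the planned number of participants need not change for this correction.

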## Introduction

1

During wakefulness, under normal conditions, our subjective experience (i.e., consciousness) is usually strongly influenced by external, environmental stimuli, that is, our consciousness is connected to the physical world [i.e., connected consciousness (CC)]. When transitioning to dream states (such as physiological dreaming or anesthesia-induced dreaming), our subjective experience often continues to be remarkably rich. Highly vivid sensory experiences during dreaming are frequently reported, yet they are usually unaffected by external stimuli, i.e., our consciousness is disconnected from the physical world [i.e., disconnected consciousness (DC)] (Figure 1). Corticocortical connections are functionally preserved to generate dreaming experiences, yet, somewhere in the thalamocortical stream, stimuli from the external world are blocked from conscious processing. Currently, a major obstacle to identify the cerebral gating mechanisms underlying sensory disconnection is the lack of behavioral differentiation between disconnected and connected conscious states in the neuroimaging literature. Previous research conducted on anesthetized participants has usually assumed a binary context, comparing brain activity acquired during wakefulness with brain activity acquired during presumed unconsciousness, where unconsciousness was inferred from participants’ unresponsiveness. Inferring the presence or absence of consciousness from (un)responsiveness^1^ has now been widely shown to be inaccurate, as unresponsiveness does not always correspond to unconsciousness (Sanders et al., 2012). Studies using the isolated forearm technique (i.e., assessing responsiveness by preventing muscle relaxants to act on one of the forearms) revealed in fact that up to 37% (Sanders et al., 2012; Linassi et al., 2018) of anesthetized patients, despite looking deeply asleep, were conscious of external stimuli (Sanders et al., 2012; Linassi et al., 2018). However, more recent estimates from clinical practice suggest that 5–10% of patients in routine clinical care experience these episodes (Sanders et al., 2017; Lennertz et al., 2023). Episodes of intraoperative dreaming are more frequent and have been estimated to occur in 22–59% of anesthetized, unresponsive patients (Leslie et al., 2007; Errando et al., 2008; Noreika et al., 2011). This implies that the supposed neural signature of consciousness gathered from classical anesthesia studies might conflate disconnected, connected consciousness, unconsciousness or the alternation between these states. We here propose that sensory perception of external stimuli can fluctuate while consciousness remains constant and independently of arousal (e.g., during dreaming), resulting in disconnected and connected dream-like experiences.

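### The single connected-versus-disconnected coefficient blends within-person and between-person contrasts, and should be accompanied by a prespecified split

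*Protocol article*

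**What the plan says.** Section 2.9.5 of the protocol article (Group-level analysis) describes a linear mixed model. "Fixed effects will be included to control for condition (CC vs. DC"), stimulus or block type, their interaction, propofol concentration and time to recovery of responsiveness (ROR). The same procedure is used for the connectivity outcomes. No term for a person's average condition is listed.

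The state, connected (CC) or disconnected (DC), comes from the person's own report after each session (2.3). Section 2.7 says that it cannot be randomised because "it is impossible to predict which individuals will report being connected and which will report being disconnected". Section 2.8 plans 40 subjects "for a total of 80 sessions (two per subject"). A person may thus be CC twice, DC twice, or once each. Some will have only one usable session: reports without recall are discarded and reports of being awake are excluded (2.3), and a failed second loss of responsiveness ends the experiment (2.2).

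The Introduction frames the question as one of changing state, proposing that "sensory perception of external stimuli can fluctuate while consciousness remains constant".

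**The concern.** A condition that varies both within and between people carries two comparisons. One sets a person's CC session against the same person's DC session. The other sets people who were always CC against people who were always DC. A single coefficient under a random intercept averages the two. The second comparison is free of bias only if a person's tendency to report tones is unrelated to that person's usual brain response.

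A random intercept for subject lowers the weight of the between-person comparison but does not remove it. If a stable trait (recall style or vascular BOLD gain, for instance) were linked both to reporting tones and to the BOLD response, the coefficient could depart from zero although no one's response changed with state. The study's interest is in the change of state, so a reader needs to know how much of the estimate comes from each source.

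**Working it through.** **1. The plan's own figure.** Inputs from 2.8: two-sided α 0.05, power 0.95, two independent groups.
- REM study, d = 0.85, ratio 1: noncentral t gives 37 + 37 = 74 (stated 74).
- NREM study, d = 0.94, ratio 0.71: 37 + 27 = 64 (stated 64).
- Propofol study, d = 1.0, ratio 2.78: 19 + 53 = 72 (stated 70; the normal approximation gives 69).
- Dropout: 74 × 1.08 = 79.9, that is 80 (stated 80).

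The sample size reproduces and is not in question. It yields 74/2 = 37 people with two usable sessions, the number used below.

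**2. Weight of the between-person part.** Let ρ be the correlation of the reported state between a person's two sessions, s²u the between-person variance of the outcome and s²e the within-person variance, with s²u + s²e = 1, so that ICC = s²u. With two sessions each and a correct subject intercept:

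W_b = [(1+ρ)/(s²e+2s²u)] / {[(1+ρ)/(s²e+2s²u)] + [(1−ρ)/s²e]}

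Example, ρ = 0.25 and ICC = 0.5: (1.25/1.5)/(1.25/1.5 + 0.75/0.5) = 0.833/2.333 = 36%.

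| ρ (assumed) | ICC 0.3 | ICC 0.5 | ICC 0.7 | people seen in both states, of 37, if half of sessions are CC |
|---|---|---|---|---|
| 0 | 35% | 25% | 15% | 18.5 |
| 0.25 | 47% | 36% | 23% | 13.9 |
| 0.5 | 62% | 50% | 35% | 9.2 |
| 0.75 | 79% | 70% | 55% | 4.6 |

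The last column is 37 × 2 × 0.5 × 0.5 × (1−ρ).

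**3. Bias when the true state effect is zero.** Assume that the state arises from a normal latent propensity, cut at its mean, with between-session latent ICC λ, and that the person part of this propensity correlates r with the person's BOLD trait. Then:
- ρ = (2/π)·arcsin(λ)
- between-person slope = √ICC · r · √λ · 0.399 / [0.125(1+ρ)]
- bias = W_b × slope

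λ = 0.7, r = 0.5, ICC = 0.5: ρ = 0.494; slope = 0.707 × 0.5 × 0.837 × 0.399/0.187 = 0.63; W_b = 0.996/(0.996 + 1.012) = 0.496; bias = 0.31 SD.

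λ = 0.1, r = 0.3, ICC = 0.5: ρ = 0.064; slope = 0.707 × 0.3 × 0.316 × 0.399/0.133 = 0.20; W_b = 0.709/(0.709 + 1.872) = 0.275; bias = 0.06 SD.

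**4. Simulation** (37 people, two usable runs, outcome ICC 0.3-0.7, true effect 0):

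| latent state ICC | correlation r | bias of pooled coefficient (SD) | rejection at nominal 5% |
|---|---|---|---|
| any | 0 | about 0 | 4-6% |
| 0 | any | about 0 | about 5% |
| 0.1 | 0.3-0.5 | 0.03-0.09 | 5-8% |
| 0.25 | 0.3 | 0.07-0.10 | 7-8% |
| 0.5-0.7 | 0.3-0.5 | 0.12-0.31 | 8-25% |

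The within-person coefficient had bias of about 0 and rejected in about 4-6%. Its standard error was about 0.19-0.40 SD, against 0.17-0.24 for the pooled one.

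**5. What the simulation leaves out.** It uses one outcome per session, omits the propofol and time-to-ROR covariates, and gives everyone two usable runs. The covariates may lower the bias. People with a single usable session add only between-person information, which raises it.

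**The case against.** The strongest reply is that the bias is conditional and that the documents give no evidence for either condition. That stands. Section 2.7 speaks of unpredictability, which does not show a stable reporting trait. At correlation 0, or with no persistence of state, the planned coefficient behaves properly. A reader might infer that stable differences between people are in fact being credited to connectedness; the documents do not support that. A stronger assumed trait link gives rejection rates of 26-67%, but those figures describe the assumption and not this trial.

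Several mechanisms are already partly handled. Hearing and memory impairments are screened out (2.1), propofol is titrated to each person's loss of responsiveness (2.2), and propofol concentration and time to ROR are covariates (2.9.5). A trait that shifts only the overall level cancels in the stimulus-by-condition interaction. A stable difference in response to sound does not cancel, since no random slope is stated.

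Nor does the plan promise a within-person contrast. The Discussion says that CC and DC are compared within one physiological state, and the sentence quoted from the Introduction is a premise, not one of Hypotheses 1-7. There is thus no contradiction in the text.

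Precision also favours the pooled estimate. At correlation 0.3 its root mean squared error was equal to or below that of the within-person estimate in every setting tried (for example 0.28 against 0.35). With 12 people seen in both states, a within-person test of d = 0.85 has 62%, 76% and 93% power at outcome ICC 0.3, 0.5 and 0.7. This argues against letting the within-person estimate decide alone whether a state effect may be claimed. It does not argue against reporting it.

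Lastly, an article condenses a fuller plan. But 2.9.5 lists the model's fixed effects, so the single coefficient is a stated choice.

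**Conclusion.** The point holds in a limited form. As stated in 2.9.5, the CC-versus-DC coefficient is a weighted mix; the between-person share is 15-79% over the assumed ranges of outcome ICC (0.3-0.7) and state correlation (0-0.75). This follows from the design and needs no assumption about traits.

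Whether the mix is biased depends on two unknowns: how persistent a person's reporting is, and how strongly it correlates with the person's BOLD response to sound or connectivity. The plausible consequence runs from none to about 0.3 SD with 25% rejection, and is small (0.03-0.09 SD, 5-8%) where persistence is weak. These figures assume a correct subject intercept and two usable runs for everyone, and they leave out the covariates.

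The pooled coefficient alone cannot show that a result reflects a change within people. It is not thereby shown to be wrong, and the sample size is untouched.

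**What to change.** In 2.9.5:
- Keep the pooled estimate as the main figure.
- Prespecify a companion model that adds each subject's proportion of usable sessions that were CC, and the product of that proportion with stimulus or block type. The CC-versus-DC terms then become within-person.
- Report the within-person and between-person estimates side by side with confidence intervals, and the number of subjects seen in both states.
- Describe the result as a within-person change of state only as far as the within-person estimate and its interval support this. Otherwise call it an association that may partly reflect differences between people.

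The cost is two model terms and one table, with no new data and no change to procedures. The drawback is the lower precision of the within-person estimate, which is why it stands beside the pooled figure and does not replace it.
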